#### 2.3.3. Secondary Outcome

Psychological well-being. The Psychological General Well-Being Index, PGWBI [79,80] will be used to evaluate subjective psychological well-being. It is a 22-item questionnaire on a 6-point Likert scale that produces a single measure of psychological well-being (total score) and a single score for six dimensions of well-being: anxiety, depression, positive well-being (i.e., satisfaction from working life and interest in the everyday activities), self-control (i.e., ability to regulates one’s emotions, behavior, desires, self-confidence and to take decisions), general health (i.e., perception of being in good health), and vitality (i.e., mental and physical fatigue, apathy, loss of energy). The PGWBI global score represents the sum of all items and ranges from 0 to 110, with higher scores indicating greater psychological well-being. Considering the Italian version, Cronbach’s alpha ranges from 0.77 to 0.88. 

Repetitive thinking. Repetitive thinking, such as rumination and worry, is a process of passive and uncontrollable thinking focused on negative content [70]. The Ruminative Response Scale, RRS [81,82], and the Anger Rumination Scale, ARS [83,84], will be used to measure depressive and anger rumination, respectively. The Ruminative Response scale is a 22-item questionnaire assessing the tendency to respond with rumination to depressed mood. The Cronbach’s alpha of the questionnaire is 0.90. The Anger Rumination Scale is a 19-item questionnaire that assesses the tendency to recall mind anger-provoking situations from the past and think about the causes and the consequences of anger episodes. In the Italian sample, the scale showed good internal consistency (α = 0.85). Moreover, the Penn State Worry Questionnaire, PSWQ [85,86], will be used to evaluate worry. It measures the tendency to worry, regardless of the specific content. The Cronbach’s alpha of the Italian version is 0.85. 

Emotional awareness. The Toronto Alexithymia Scale-20, TAS-20 [87,88] will be used to evaluate emotional awareness, namely, the ability to distinguish, recognize, and communicate emotions [89]. The TAS-20 is composed of three scales: difficulty describing feelings, difficulty identifying feelings, and the externally oriented thinking. It also provides a total score of alexithymia. The Cronbach’s alpha for the total score in the Italian version is 0.81. 

Imagined interaction. The Scale of Imagined Interaction, SII [90] evaluates the eight attributes (frequency, proactivity, retroactivity, discrepancy, variety, valence, self-dominance, and specificity) and the six functions (relational maintenance, compensation of real interaction, rehearsal, self-understanding, conflict, catharsis) of imagined interaction. The questionnaire begins with a brief explanation of what imagined interaction is; it comprises 60 items on a 7-point Likert scale, ranging from very strongly disagree to very strongly agree, and seven open questions about qualitative contents of the imagination. Considering the original version, Cronbach’s alpha ranges from 0.70 to 0.91 for the attributes dimensions and 0.71 to 0.90 for the frequency dimensions. The scale has been translated and back-translated into Italian. 

#### 2.3.4. Other Measures

Sociodemographic Questionnaire. An ad-hoc questionnaire will be used to collect information about the residence, professional status, psychological past/current treatment, and educational level.

Feedback questionnaire. An ad-hoc questionnaire will be proposed to collect feedback and suggestions from participants in the ComunicaBene condition. It includes 26 items, with five open questions and 21 on a 5-point Likert scale. The questionnaire aims to collect information about the experiences with the Tutor, the general utility of the training, the acceptability, and the feasibility of the contents and activities. Please see Section S1 in the Supplementary Materials for the entire questionnaire.

Treatment fidelity questionnaire. After every meeting, the Tutor will have to complete an ad-hoc questionnaire to ensure the treatment fidelity was guaranteed [91]. The questionnaire is composed of 10 questions: 7 open questions (e.g., “issues discussed during the meeting”, “difficulties reported by the students”); 1 yes or no question (i.e., “the student was in touch with you between the meetings?”); and 2 multiple choice questions (i.e., “module discussed during the meeting”, “duration of the meeting”). 

### 2.4. Procedure

Every participant will first sign the institutional consent forms, including the study’s goals, procedure, risks, and data protection and privacy information according to the General Data Protection Regulation (EU) 2016/679 (GDPR). Once achieved, each participant will receive a username and password to log in to their private page on the website. Participants will find a first assessing module containing the sociodemographic questionnaire and the SCL-90-R and WHODAS 2.0 questionnaires to detect clinical disorders. Based on the exclusion criteria, in the absence of any significant clinical condition, participants will be randomly assigned to either the ComunicaBene or Waitlist condition. Before, at the end, and 6 months after the end of the intervention, participants will complete a series of standardized questionnaires to assess assertiveness (SIB-S), psychological well-being (PGWBI), depressive rumination (RRS), anger rumination (ARQ), worry (PSWQ), alexithymia (TAS-20), and imagined interaction (SII). Moreover, an ad-hoc questionnaire will also be administered at the end of the intervention to evaluate satisfaction with the program. Every participant will find the questionnaires on their private page on the website.

#### 2.4.1. ComunicaBene Condition 

Participants in this condition will use their username and password to log in to their private page on the website. ComunicaBene provides different online training modules that are presented in three consecutive phases. Below, an outline for each step is presented. 

(1) Psychoeducation and motivation. This phase aims to help students recognize and distinguish their own and others’ communication styles (assertive, passive, or aggressive), understand and learn the principles of assertive communication, and develop awareness about their own needs and emotions, especially the one that can be an obstacle to communicate assertively [3]. At first, participants will be encouraged to set specific goals (e.g., “I would like to improve the ability to say no to my parents”; “I would like to be able to express my disagreement to my Supervisor”) that they want to achieve with the program, focusing on the most challenging interpersonal situations, such as the factors that hinder assertive communication, and the cost and benefits of changing. Later, they will find theoretical and practical content about needs, emotions, communication style, and assertiveness. Also, they will have to report their significant interaction in a personal diary [1]. Moreover, this phase also includes a preparation session to allow students to train their imaginative skills. The participant will be asked to recall a specific, concrete, and real memory or to imagine future actions [51]. 

(2) Imagery sessions. Participants will find thirty audio tracks that have been developed ad hoc, based on typical interpersonal problems of the target population (an example of audio track is available under request to the corresponding author). Since assertiveness is a situation-specific behavior and can be affected by personal, situational, and interactional influences [92], every track is content-interlocutor-specific. In particular, there are six possible situations (express disagreement, decline a request, make a request, express constructive criticism, handle criticism, and express positive emotions) combined with five interlocutors (partner, friends, familiar, colleagues, and superior). Every track will be listened to twice, starting with the easiest situation [52]. Each audio track includes a guided imagery technique in which a voice guides individuals through evoking specific interpersonal situations. This technique, based on process and end-state imagery [93], helps participants in focusing on the necessary steps for assertive communication (process imagery) and visualizing the desired outcome (end-state imagery). In particular, every audio track is composed of eight phases: (1) pre-relaxation phase, (2) introduction of the situation and questions to create vivid and realistic mental imagery, (3) imagination of their spontaneous response with associated consequences, (4) instruction for the assertive response, (5) repetition of the assertive response with the guide, (6) repetition of the assertive response without the guide, (7) focus on the consequences of assertiveness, and (8) conclusion. Every audio tracks last about 10 min. After every listening, students will complete an ad-hoc journal to stimulate a post-audio track reflection [1]. The journal includes questions to identify feelings experienced before, during, and after the imaginative session, investigate the degree of satisfaction with the session, and identify the negative thoughts haven during the session. Students are especially helped to identify cognitive biases, irrational thoughts, and catastrophic scenarios. Lately, students have been helped to replace negative thoughts and scenarios with alternative and more realistic ones [94]. 

(3) Learning generalization. This phase aims to ensure learning generalization by asking students to present what they learned during imaginative practice sessions in real-life situations. Students will have to monitor their significant interactions using a self-monitoring tool.

The program includes periodical supervision via a Tutor. The Tutors will be psychologists previously trained in delivering the intervention, using the platform, and becoming familiar with CBT and NVC models. In particular, the Tutor will have to maintain and stimulate motivation and commitment, monitor the student’s progress on the website, and set a video-call meeting every week with their students. During the online meeting, Tutors and students will review the activities, discuss the most critical content, explain unclear concepts, and address any difficulties encountered. Moreover, the Tutor will have a modeling role: it can interpret the communicator and serve as a model of assertive behavior [95]. Lastly, the Tutor will have to realistically reinforce participants’ effort and success and constructively criticize dysfunctional behaviors [96]. Every Tutor will have to adhere to an ad-hoc protocol created for the intervention to guarantee treatment fidelity (Please see Section S2 in the Supplementary Materials for the entire protocol). Moreover, Tutors will be periodically supervised by an expert psychotherapist who is also the creator of the intervention. Please refer to Figure 2 for a timeline of the intervention.

#### 2.4.2. Waitlist Condition

Participants in this condition will not receive training but return for the post-intervention and follow-up assessment. After the study ends, participants will be invited to participate in the intervention.

## 3. Statistical Analysis

SPSS (IBM) version 27 will be used to process data. Descriptive analyses will be run on sociodemographic variables, data related to the satisfaction questionnaires, and SCL-90-R and WHODAS 2.0 scores. Chi-Square tests and Student’s *t*-tests will be run to investigate differences between participants in the two conditions on baseline demographic variables, gender variables, age, and all baseline measures. If some variables significantly differ between conditions, they will be considered as covariants in the following analyses. A series of mixed models of analysis of variance (ANOVAs) will be run to investigate the efficacy of the intervention on the SIB-S, PGWBI, RRS, ARQ, PSWQ, TAS-20, and SII scores, as a function of the factor between CONDITION (ComunicaBene vs. Waitlist) and the factor within TIME (Baseline vs. Post-Intervention vs. Follow-Up). The level of significance will be set at *p* < 0.05. Effect sizes will be calculated using partial eta squared and interpreted based on benchmarks that Cohen (2013) suggested: η_p_^2^ = 0.01, small effect size; η_p_^2^ = 0.06, medium effect size; η_p_^2^ = 0.14 large effect size. The post hoc analyses of significant interaction will be conducted using the LSD post hoc test.

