#### 2.3.2. Primary Outcome

Assertiveness. The Scale for Interpersonal Behavior-Short Form, s-SIB [78], will measure assertive behavior. It is a 50-item questionnaire divided into two main scales (25 items each): distress and performance, which measure the distress in state assertiveness and the probability of engaging in a specific assertive behavior, respectively. Moreover, each scale consists of five dimensions: negative assertion (i.e., requesting a change in others’ behavior, defending one’s rights and opinions, refusing requests), personal limitation (i.e., admitting one’s failures, faults, and shortcomings), initiating assertiveness (i.e., introducing oneself, starting conversations, expressing opinions), positive assertion (i.e., praising others, accepting compliments, displaying positive feelings), and general assertiveness. The Italian version showed good internal consistency with alpha coefficients ranging from 0.71 to 0.90 for the distress scale and 0.67 to 0.85 for the performance scale. 

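### Covariates are chosen by baseline significance tests between randomised arms, so chance sets the efficacy model, and baseline s-SIB becomes a covariate only if its own test is significant

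*Protocol article*

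**What the plan says.** The protocol article, section 2.4 (Procedure), states that "participants will be randomly assigned to either the ComunicaBene or Waitlist condition". Section 3 (Statistical Analysis) then plans chi-square and Student's t-tests for "differences between participants in the two conditions on baseline demographic variables, gender variables, age, and all baseline measures". The rule that follows is: "If some variables significantly differ between conditions, they will be considered as covariants in the following analyses". No covariate is named in advance.

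The same section analyses each outcome by a mixed ANOVA with CONDITION as the between factor and "the factor within TIME (Baseline vs. Post-Intervention vs. Follow-Up") as the within factor. The only significance level given is 0.05, and no separate threshold is set for the baseline tests.

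Section 2.3.2 makes the s-SIB the primary outcome. Its baseline value is one of the baseline measures, so it is among the variables screened.

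**The concern.** With proper randomisation, any baseline difference between arms is due to chance. A significance test on it cannot show whether the variable predicts the outcome, which is the reason to adjust. The rule can therefore add a variable of no prognostic value and leave out a strong predictor whose imbalance falls just short of significance. The wording, under which flagged variables are to be considered, leaves further discretion once the data are seen.

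There is also a structural conflict. Baseline is a level of TIME, so a flagged baseline s-SIB would be a covariate in a model whose outcome already contains the same values. The article does not reconcile the two uses. Whether the primary analysis compares change from baseline or adjusts by covariance then depends on one chance p-value.

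At stake are a fixed primary model, an error rate that does not depend on the imbalance seen, and the precision available from a baseline score that is collected anyway.

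**Working it through.** **Inputs from the article.** Two arms and three time points; f = 0.21, 95% power, two-sided 5%, minimum N = 60, drop-out about 25%, about 90 recruited (Sample Size Calculation); significance level 0.05 (section 3).

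**Assumptions, not in the article.** 1:1 allocation; equal correlation r between all pairs of time points, taken as 0.5 and 0.7; a sustained effect of 0.5 SD at both later visits.

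**1. The plan's own figure.** For the CONDITION × TIME interaction, λ = f²·N·3/(1 − r) = 0.0441 × 60 × 3/0.5 = 15.88, with 2 and 116 degrees of freedom. Power is 0.950, so N = 60 reproduces at r = 0.5. It presumes baseline as one of three time points and no covariate.

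**2. How often chance selects a covariate.** For k independent tests, P(at least one) = 1 − 0.95^k.

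| k | P(at least one) | Expected number |
|---|---|---|
| 9 (seven instruments, gender, age) | 37% | 0.45 |
| 12 | 46% | 0.60 |
| 15 | 54% | 0.75 |
| 20 | 64% | 1.0 |
| 38 (all scales and subscales of the outcomes) | 86% | 1.9 |

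The article does not say which scores are tested. Scores within an instrument are correlated, so 86% is an upper extreme.

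**3. Imbalance needed to flag baseline s-SIB.** The threshold is t(0.975, 2n − 2)·√(2/n). It is 0.52 SD with 30 per arm and 0.42 SD with 45 per arm.

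**4. What happens below the threshold.** The interaction compares change from baseline, which subtracts the whole imbalance. At correlation r only the fraction r of a baseline difference is expected to persist, so the comparison over-corrects by (1 − r) × imbalance. For 0.4 SD this is 0.5 × 0.4 = 0.20 SD at r = 0.5 and 0.3 × 0.4 = 0.12 SD at r = 0.7.

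**5. Type I error, by simulation.**
- Overall, with baseline s-SIB the only candidate covariate: 4.3–4.7% under the plan's rule, 5.0–5.2% for the mixed ANOVA with no covariate, 4.7–5.3% when baseline is always a covariate.
- Conditional on the imbalance (30 per arm, r = 0.5, interaction test without covariate): about 3% at zero, about 4% at 0.2 SD, 7–8% at an unflagged 0.4 SD.

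**6. Precision, like for like.** The contrast is the mean of both follow-ups, one degree of freedom, 30 per arm. The variance per participant is (1 + r)/2 + 1 − 2r for change from baseline and (1 + r)/2 − r² with baseline as covariate. SE = √(2·variance/30), and power comes from the noncentral t with noncentrality 0.5/SE.

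| r | Analysis | Variance | SE | 0.5/SE | Power |
|---|---|---|---|---|---|
| 0.5 | Change | 0.75 | 0.224 | 2.24 | 59% |
| 0.5 | Baseline-adjusted | 0.50 | 0.183 | 2.74 | 77% |
| 0.7 | Change | 0.45 | 0.173 | 2.89 | 81% |
| 0.7 | Baseline-adjusted | 0.36 | 0.155 | 3.23 | 89% |

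For the two-degree-of-freedom interaction test, simulation gives these powers, first with baseline s-SIB always a covariate and then under the plan's rule: 57% and 48% (r = 0.5, 30 per arm), 79% and 68% (r = 0.5, 45 per arm), 78% and 73% (r = 0.7, 30 per arm), 93% and 90% (r = 0.7, 45 per arm).

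**The case against.** The strongest reply is that baseline is already handled, and four stronger readings do fail.

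- **Baseline s-SIB is ignored unless significant.** A reader might infer this from the selection rule, but section 3 makes baseline a level of TIME, so the interaction always compares change from baseline. Only covariate adjustment hangs on the p-value. For the same reason an unflagged imbalance is over-corrected rather than left uncorrected.
- **The rule inflates type I error.** It does not: the overall rate is 4.3–4.7%. The high conditional rates are offset by low ones near zero imbalance. They are also uncommon: baseline tests precede drop-out, and with 45 per arm an unflagged difference of 0.4 SD or more arises in about 1% of trials (7.6% with 30 per arm).
- **The power loss runs from 49% to 77%.** Setting the planned interaction test (49%) against the adjusted mean of both follow-ups (77%) mixes a two- with a one-degree-of-freedom test. The one-degree-of-freedom change contrast already reaches 59%, so only the step from 59% to 77% is due to adjustment, and at r = 0.7 it shrinks to 81% against 89%.
- **Thirty-eight scores are tested.** The article does not say so, and with nine tests the chance of a spurious covariate is 37%.

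It is also fair that naming covariates in advance, without changing TIME, would already answer the charge of a data-dependent model. It would not resolve the double role of baseline s-SIB.

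What the reply leaves untouched is that the covariate set is decided by chance, the double role is unreconciled, and precision is lost. This is a rule the article states, not a detail left to a fuller plan.

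**Conclusion.** The point holds in this form. Section 3 lets baseline significance tests between randomised arms choose the covariates, so the efficacy model is not fixed in advance. Baseline s-SIB always enters as a level of TIME, but as a covariate only when its test is significant, and then in two roles at once.

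The main measurable cost is precision: 18 percentage points of power at r = 0.5 and 8 at r = 0.7, for the mean of both follow-ups with 60 participants. Error that depends on the observed imbalance is a secondary cost, and the trial-wide error rate is sound.

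These sizes rest on the assumed correlations, 1:1 allocation, equal correlation over time and a sustained 0.5 SD effect, none of which the article states. The 0.05 screening threshold is inferred from the general significance level. The faults in the rule itself need none of these sizes.

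**What to change.** Before outcome data are examined:

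1. Delete the baseline significance tests and the covariate-selection sentence from section 3.
2. Describe baseline characteristics by arm without p-values.
3. Pre-specify that each efficacy model adjusts for the baseline value of its own outcome, whatever the imbalance, with TIME limited to post-intervention and 6-month follow-up.

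No new data or participants are needed. The one further cost is in the Sample Size Calculation: it is written for a mixed ANOVA with three time points and must be re-expressed for the revised model, with the assumed correlation stated.

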## 2. Materials and Methods

### 2.1. Study Design

A randomized control trial will be conducted, in which participants will be randomly allocated to an experimental or control condition. The ComunicaBene condition will consist of guided self-help imaginary training to improve assertiveness. The Waitlist, or control, condition will consist of a waiting list. Participants will receive the same intervention as those in the ComunicaBene condition but at a later time. Assessment will be run at baseline (pre-intervention assessment), at the end of the intervention (post-intervention assessment), and six months after the intervention (follow-up assessments). Please see Figure 1 for the design and participant flow chart.

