#### Sample Size Calculation

The sample size has been estimated based on power analysis using G*Power 3.1. [72]. The following parameters were set on the sample size calculator: effect size of f = 0.21, mixed analysis of variance (ANOVA) including within-subject (3-time points), and between-subject (2 groups); effects were with 95% power and at a two-sided 5% significance level. Results suggested that the minimum required sample size was 60 participants. However, considering the percentage of drop-out occurring in Internet-based intervention for university students [73], a drop-out rate of around 25% was expected. For this reason, it is planned to recruit approximately 90 participants.

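### The planned mixed ANOVA by default uses only participants with all three assessments, and the expected 25% drop-out is met only by over-recruitment, leaving the randomised comparison open to bias

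*Protocol article*

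**What the plan says.** Section 2.1 describes a randomised comparison in which "participants will be randomly allocated to an experimental or control condition", with assessments at baseline, post-intervention and six months.

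Section 3 gives one efficacy method: "A series of mixed models of analysis of variance (ANOVAs) will be run to investigate the efficacy of the intervention". The between factor is condition, the within factor is time at three levels, the software is SPSS 27, the effect measure is partial eta squared, and significant interactions are followed by LSD tests. It names no analysis set and no rule for missing scores.

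The Sample Size Calculation uses the same model: a mixed ANOVA with three time points, two groups and f = 0.21, where "effects were with 95% power and at a two-sided 5% significance level". "Results suggested that the minimum required sample size was 60 participants". It adds that "a drop-out rate of around 25% was expected" and sets recruitment at about 90 for that reason.

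On timing, section 2.4 says: "Before, at the end, and 6 months after the end of the intervention, participants will complete a series of standardized questionnaires".

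On workload, section 2.4.1 gives ComunicaBene participants thirty tracks of about 10 minutes ("Every track will be listened to twice"), a journal entry after each listening, and weekly tutor calls. Under section 2.4.2, waitlist participants only return for assessments.

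**The concern.** A repeated-measures ANOVA with a three-level within factor needs all three scores from each person; in SPSS a participant who lacks one is removed entirely. The plan expects a quarter of participants to drop out, and its only response is to enrol more. That protects the number analysed. It does not protect the comparison of the groups as randomised.

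If people leave for reasons linked to how they are doing, and this differs between arms, those who remain are no longer comparable. The workload falls on one arm only, and the Discussion itself notes that the tracks may not suit everyone and that trouble with immersion could weaken the effect. Differential loss is therefore plausible, though not established. At stake is the main efficacy claim, together with baseline and any post-intervention scores already collected from people who later leave.

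**Working it through.** **1. Which analysis is meant.** For the condition-by-time interaction the noncentrality is λ = f² × N × m / (1 − ρ), with df 2 and (N − 2) × 2.
- From the plan: f = 0.21, m = 3 time points, 2 groups, 5% level, 95% power.
- Assumed, because not stated: ρ = 0.5 between time points, and sphericity.
- At N = 60: λ = 0.0441 × 60 × 3 / 0.5 = 15.876, df 2 and 116, power 0.950. The plan's 60 is reproduced.
- The between-groups test at the same ρ would need 200.

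The trial was therefore sized for the interaction in a classical repeated-measures ANOVA, which agrees with the effect measure in section 3.

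**2. How many would leave.**
- 90 × 0.75 = 67.5 remain, so 22 or 23 of 90 are lost. This takes each drop-out to miss at least one assessment.
- Needed to keep 60: 60 / (1 − 0.25) = 80, below 90.
- Power with 68 analysed is about 97% at ρ = 0.5.

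**3. Workload by arm.** 30 tracks × 2 listenings × 10 min = 600 min, or 10 hours of audio, plus journals and calls, against assessments only on the waitlist.

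**4. What loss could do.** None of these inputs comes from the document:
- no true effect; scores with SD 1, higher is better, ρ = 0.5;
- log-odds of drop-out falling by 1 per SD of change from baseline to post-intervention wherever drop-out is outcome-related;
- bias = mean change among ComunicaBene completers minus that among waitlist completers.

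| Drop-out ComunicaBene / waitlist | Related to outcome in | Completer bias, post | Completer bias, follow-up |
|---|---|---|---|
| 40% / 10% | neither arm | about 0 | about 0 |
| equal rates | both arms, same mechanism | about 0 | about 0 |
| 25% / 25% | ComunicaBene only | +0.21 SD | +0.11 SD |
| 40% / 10% | both arms, same slope | +0.24 SD | +0.12 SD |
| 40% / 10% | ComunicaBene only | +0.33 SD | +0.16 SD |

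With 45 per arm, the nominal 5% interaction test was false-positive in 20–21% of trials in the last row and 10–11% in the third. With the slope halved, the rates are 9–10% and 7%.

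**5. What a mixed model would recover.** If every drop-out has a post-intervention score and misses only follow-up, a model using all observed scores has bias of about 0, because the loss depends on something observed. If drop-outs miss both later assessments, the model keeps +0.26 SD at post (40%/10%, ComunicaBene only) or +0.17 SD (25%/25%, ComunicaBene only). It removes (0.33 − 0.26)/0.33 = 21% and (0.21 − 0.17)/0.21 = 19% on these rounded figures, so about a fifth to a quarter. At follow-up it removes about half.

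**The case against.** **Completers-only analysis is not stated.** A reader might infer that the plan declares one. It does not; this follows from the procedure named. Imputation before the ANOVA would be compatible with section 3, and a fuller plan might provide it. This stands as a limit on certainty. It does not dispose of the point, because the concern is with the method the article fixes: run as described it drops incomplete cases, and the sample-size section treats drop-outs as lost.

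**The wording could mean a linear mixed model.** The name in section 3 allows that reading, but the sizing, the factor layout and partial eta squared point to repeated-measures ANOVA.

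**People who skip modules are not excluded.** It is tempting to say that efficacy is estimated only in those who finish a demanding programme. The documents do not support that. The ANOVA removes people with a missing questionnaire. Section 2.4 attaches no adherence condition to the later assessments, and waitlist participants attend them without any modules. Whether someone who stops early is still assessed at the end of the intervention is unclear; the timeline figure is not available.

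**Unequal, outcome-related loss is an assumption.** This stands. No arm-specific rate is given, the Discussion calls the programme short and expects tutors to sustain adherence, and waitlist participants may leave too. A firm statement that the result will favour ComunicaBene would go beyond the document.

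**The sample is large enough.** This also stands: 80 are needed and 90 are planned.

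**Conclusion.** The point holds as a weakness of the stated method. Run by default, the between-within ANOVA would remove about 22 of 90 randomised participants from the efficacy comparison at the drop-out rate the plan expects, and over-recruitment addresses power only.

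The resulting bias cannot be sized or signed from the document. On the assumed inputs, bias at post-intervention is about 0 when drop-out is unrelated to outcome or follows the same mechanism in both arms, and about +0.2 to +0.3 SD when it follows poor change in ComunicaBene only. The conclusion assumes that SPSS is run without prior imputation and that drop-outs miss at least one assessment.

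A reader might also infer that a mixed model would cure the problem. It does so only where loss depends on scores that were observed, so changing the model is necessary but not sufficient.

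**What to change.** - **Analysis.** Replace the ANOVA by a linear mixed model for repeated measures (SPSS MIXED, REML, unstructured covariance) on all randomised participants as allocated, using every available score. The unstructured covariance also removes the sphericity assumption.
- **Data collection.** Invite everyone, including those who stop the modules, to both later assessments, at matched times after randomisation in the two arms.
- **Reporting.** Show drop-out by arm and by assessment.
- **Sensitivity analysis.** Add one in which missing ComunicaBene scores are set at the waitlist level.

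The second and fourth items matter because the mixed model recovers little at post-intervention when that score is itself missing.

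The cost is revised analysis wording, a different procedure in the same software, slightly more analysis work and reminder e-mails to non-completers. Mixed-model estimates would be reported in place of partial eta squared. No additional participants are needed.
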